#### Transthoracic echocardiography

A comprehensive transthoracic echocardiogram (iE33; Philips, Eindhoven, the Netherlands) will be performed at rest with the subject in the left lateral decubitus position by a single experienced sonographer using second harmonic imaging and an S5-1 multifrequency transducer. All parameters will be measured in triplicate and averaged as per the American Society of Echocardiography guidelines.^55^ Analysis will be performed offline by a single blinded observer on an Xcelera workstation (Philips). Ventricular dimensions, wall thickness, chamber volumes, and stroke volume will be determined using standard methods.^56^ Left ventricular diastolic function will be determined using standard techniques.^57^ Peak systolic (*s*′), early diastolic (*e*′), and late diastolic (*a*′) mitral annular velocities will be measured at end-expiration at the septal, lateral, inferior, and anterior LV walls with real-time pulsed wave tissue Doppler imaging (TDI).^58^

Gray-scale images for 2-dimensional LV strain, strain rate, and torsion will be acquired in cineloop format in triplicate from the apical 4-, 2-, and 3-chamber views and parasternal short-axis views at basal, mid, and apical levels at end expiration at frame rates >70 Hz for offline analysis using commercially available software (QLAB; Philips). Myocardial contours will be manually traced at end-systole, and the software will then generate a region of interest over the myocardium. This will enable frame-to-frame tracking of ultrasonic speckles that change position according to surrounding tissue motion throughout the cardiac cycle. Peak systolic velocities, strain, strain rate, rotation, and twist will be measured for each myocardial segment in triplicate and averaged.

In those subjects with appropriate image quality, transthoracic echocardiography will also be performed during a progressive submaximal exercise test to derive stress-related changes in LV systolic and diastolic function using TDI and strain measures. Subjects will be installed on a dedicated semisupine cycling ergometer (Schiller ERG 911 BP/L, Baar, Switzerland). After a 15-minute rest period, each subject will undergo an exercise test that includes 3 workload stages of 4-minute duration at 20%, 30%, and 40% of their maximal aerobic power estimated via the Wasserman equation [(body mass (50.72 − 0.372 × age)) − 350]/10.3 and corrected for semisupine position (20% removed from normal values).^59^, ^60^

### The KARMA study: effect of *K*idney don*A*tion on bone-mine*R*al *M*etabolism and *A*rterial stiffness

Participants enrolled into the study at Addenbrooke's Hospital, Cambridge, will undergo a more detailed biochemical assessment of the bone mineral axis together with dual-energy x-ray absorptiometry (DEXA). It is planned to recruit 99 participants for the KARMA study, 2 controls for every living donor (online Supplementary Table II).

#### Dual-energy x-ray absorptiometry scan

Dual-energy x-ray absorptiometry is a means of measuring bone mineral density and soft tissue composition. A beam of x-ray, filtered into 2 energy bands, passes through the patient's body. When soft tissue absorption is subtracted out, the bone mineral density can be determined from the absorption by bone at each energy. Dual-energy x-ray absorptiometry is the most widely used and most thoroughly studied bone density measurement technology. For kidney donors, DEXA scans of the total body, hips, and lumbar spine scanning will be performed before surgery and 1 year later. The total body scan will enable any changes in muscle mass to be estimated and their influence on bone density factored out of the bone density analysis. The total effective dose of x-ray radiation for the proposed scans will be approximately 4.5 μSv, comparable with a daily background from atmospheric sources of 6 μSv. Pregnancy testing (urinary β-human chorionic gonadotropin) will be performed in female participants of childbearing age in the donor group before DEXA scanning.

### Blood tests

These will be the same as for the main EARNEST study, but for kidney donors, additional samples will be taken at days 1, 2, and 3 postoperatively and 6 weeks after donation. Blood samples will be centrifuged within 30 minutes of venesection, and serum and plasma were separated and frozen at −70°C. Samples will later also be used for testing of vitamin D metabolites (1, 25-, and 25-vitamin D), FGF-23, Klotho, PTH, osteoprotegerin, receptor activator of nuclear factor κB ligand, bone remodeling markers (carboxy-terminal collagen cross-links, N-terminal propeptides of type I procollagen, osteocalcin), and Fetuin-A as well as renin and aldosterone.

#### Urine tests

Again, these will be the same as for the main EARNEST study, but in addition for kidney donors, 100 mL aliquots of urine will be taken at days 1, 2, and 3 postoperatively and 6 weeks after surgery and frozen at −70°C for later measurement of Fetuin-A, calcium, and phosphate.

### Statistical analysis

The formal comparison between arms of each of the coprimary end points will use a linear regression model on the within-patient change from baseline, adjusting for baseline value, sex, ethnicity, use of antihypertensives, age, eGFR at donation (and iGFR where available in donors), and the other coprimary end point at baseline. To formally control the overall significance level over both coprimary end points (aPWV and blood pressure) at 5%, a Holm-Bonferroni method will be used. Findings will be interpreted taking into consideration that aPWV and blood pressure are correlated. A secondary analysis of the coprimary end points will be performed according to age, ethnic group, baseline eGFR and change in eGFR (and isotopic GFR where available in donors), BMI, and predonation hypertension.

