### Study protocol

A flowchart of the study protocol is presented in the Figure. Investigations will be performed in all participants at baseline in controls and within the 6 weeks before nephrectomy in donors, with subsequent follow-up studies performed at 12 months. Kidney donors will undergo routine follow-up by their local medical and surgical team with no alteration to normal care. No restrictions will be made to the introduction of any treatment including antihypertensive drugs. At baseline and follow-up visits, body mass index (BMI), blood pressure, heart rate, and any clinical events will be recorded.

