#### Training and reproducibility

Delegated study staff will receive formal training in measurement techniques of arterial stiffness and undertake a reproducibility and measurement quality study before study commencement. Measurements at each center will only be performed by dedicated staff who have undergone this training. Equipment will be calibrated at baseline and throughout the study at specific intervals.

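### The coprimary models leave out centre in a non-randomised multicentre comparison with an unequal planned ratio at one centre: a modest risk of bias, mainly for aPWV, that is cheap to remove

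*Protocol article*

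**What the plan says.** All references are to the protocol article.

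- **Model.** Statistical analysis: the formal comparison of each coprimary end point is described as "adjusting for baseline value, sex, ethnicity, use of antihypertensives, age, eGFR at donation". To these the section adds isotopic GFR for donors who have it, and the baseline of the companion coprimary measure. The method is a "linear regression model on the within-patient change from baseline". Centre appears nowhere in that section. BMI appears there only as a factor in the secondary analysis.
- **Design.** Study design and Study population: a non-randomised comparison of 440 donors and 440 controls at seven core centres, with more allowed to join. Controls come from the same clinics as donors and, where suitable, from donors' families. They are described as matched, but the matching factors are not named.
- **Measurement.** Training and reproducibility: "Measurements at each center will only be performed by dedicated staff who have undergone this training". Staff must also "undertake a reproducibility and measurement quality study before study commencement", and equipment is recalibrated at intervals.
- **Ratio at one centre.** The KARMA study, run among main-study participants at Cambridge: "It is planned to recruit 99 participants for the KARMA study, 2 controls for every living donor".
- **BMI.** Study protocol: "At baseline and follow-up visits, body mass index (BMI), blood pressure, heart rate, and any clinical events will be recorded". The Discussion also names BMI among the influences that the study intends to examine.

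**The concern.** Without randomisation, nothing balances donors and controls across centres except recruitment practice, so the regression model carries most of the protection. The design uses the clinic to make the groups comparable, but the analysis does not use it.

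One centre has a planned ratio of 1:2 inside a study that is 1:1 overall, so group and centre are associated to some degree by plan. If mean 12-month change at that centre differs from the rest for reasons unrelated to donation, such as a change of operator technique or device between visits, part of that difference is attributed to donation. An upward drift at Cambridge would raise the control mean more than the donor mean and could mask harm. A downward drift could create the appearance of harm. The study is built to detect an aPWV difference of only 0.22 m/s, so a modest bias could matter.

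**Working it through.** **The plan's own figure.** Inputs from EARNEST power calculations and sample size: SD of change 1.0 m/s, difference 0.22 m/s, two-sided 2.5%, power 80%, dropout 9%.

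- n per group = 2 × (2.241 + 0.842)² × 1.0² / 0.22² = 393. The plan uses 400, which gives 80.8% power.
- 400 / 0.91 = 440 recruited per group.
- The ratio 2.2/10 for blood pressure is the same, so the result is the same.

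The sample size reproduces, and this point does not affect it.

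**Group by centre.** From 99 participants at 2 controls per donor: 99/3 = 33 donors and 66 controls. Assume that these are all of Cambridge's participants and that they count within 440:440.

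- Other centres: 440 − 33 = 407 donors and 440 − 66 = 374 controls.
- Cambridge share: 33/440 = 7.5% of donors and 66/440 = 15.0% of controls.

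**Bias without a centre term.** Bias = (donor share − control share) × drift = (0.075 − 0.150) × drift = −0.075 × drift. Drift here is the extra mean 12-month change at Cambridge relative to the other centres, unrelated to donation. The documents give no drift, so a range is assumed for aPWV:

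| Assumed drift (m/s) | Size of bias (m/s) | Share of 0.22 m/s |
|---|---|---|
| 0.1 | 0.008 | 3% |
| 0.5 | 0.038 | 17% |
| 1.0 | 0.075 | 34% |

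**Effect on the test.** 1,000 null trials were simulated per scenario: 400 per group, 33 donors and 66 controls at one centre, SD of change 1.0 m/s, regression on group and baseline, nominal 2.5%. The baseline distribution (mean 7, SD 1.2 m/s, plus measurement error) is an assumption. With 400 per group, the difference in shares is 33/400 = 8.25 percentage points, so the biases are slightly larger than in the table above.

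| Scenario at that centre | Mean effect, no centre term | Rejection | Mean effect, centre term | Rejection |
|---|---|---|---|---|
| No offset, no drift | 0.0026 | 2.8% | 0.0027 | 2.5% |
| Constant offset 1 m/s | −0.0189 | 3.0% | 0.0017 | 1.8% |
| Drift 0.5 m/s | −0.0429 | 5.5% | −0.0018 | 1.6% |
| Drift 1.0 m/s | −0.0845 | 13.5% | −0.0020 | 2.2% |
| Offset 1 and drift 0.5 m/s | −0.0550 | 7.0% | 0.0041 | 2.6% |

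Simulation error near 2.5% is √(0.025 × 0.975 / 1000) = 0.5 percentage points, so 3.0% cannot be told apart from nominal.

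**Cost of the term.** The correlation of group with the Cambridge indicator is (33 × 374 − 66 × 407) / √(99 × 781 × 440 × 440) = −0.119. The variance inflation is 1 / (1 − 0.119²) = 1.014. In the simulations the standard error was about 0.067 with the term, against 0.066 to 0.070 without it.

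**The case against.** The case on the other side is substantial, and much of it stands.

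- **The outcome is a change score.** A fixed difference between staff, devices or centres largely cancels. A constant 1 m/s offset left a bias of only about 0.02 m/s. Only drift between visits matters, and none is documented. This stands.
- **The protocol acts against drift.** Common training, a reproducibility study before the start and repeated calibration all reduce it, and two years of staggered recruitment make one centre-wide shift less likely. Drifts of 0.5 and 1.0 m/s are half and all of the assumed SD of individual change, so they are the upper part of the range. This stands.
- **The unequal ratio is documented for one substudy only.** A reader might infer that the ratio differs across centres generally. The documents give no ratio for any other centre, and recruiting controls from the donors' own clinics works against such separation.
- **Blood pressure.** A reader might carry the drift argument over to both coprimary end points in equal measure. Ambulatory pressure comes from an automated recorder, so operator technique matters much less, and no blood-pressure drift is at hand.
- **BMI.** A reader might infer that group is confounded with BMI. The documents show only that BMI is recorded and left out of the primary models. They show no difference between the groups, both groups face the same eligibility criteria, and BMI is used in the secondary analysis.
- **Precision.** A reader might expect leaving out centre to inflate the residual variance materially. The nearly unchanged standard error does not support that.

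What does not stand is that the omission merely reflects a condensed article. The article states the covariate list for the formal comparison, and that list lacks centre.

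**Conclusion.** The point holds as a risk of bias, mainly for aPWV. The stated coprimary models leave out centre in a non-randomised study of at least seven centres, with centre-specific staff and one planned 1:2 ratio inside a 1:1 study. The bias is about 7.5% of any Cambridge-specific drift. That is trivial at 0.1 m/s and up to about a third of the target difference at 1.0 m/s.

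The size rests on three assumptions: that the 99 substudy participants are all of Cambridge's participants, that they count within the 440:440, and the drift values themselves. The documents do not support saying that the donor effect is biased, or that BMI confounds it. For BMI, the case is only that a recorded variable, which the protocol itself names as of interest, could be adjusted for as a precaution. Using it in a secondary analysis does not adjust the main donor effect.

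**What to change.** Add centre as a fixed effect to both coprimary models, with a rule written in advance for pooling very small centres, since more may join. Add baseline BMI as a precautionary covariate, without stating that it differs between the groups. Specify both before outcome data are examined, because a later addition would look driven by the results. If the analysis plan already includes centre, bring the two covariate lists into agreement.

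Cost: no new data. Seven centres take 6 degrees of freedom and BMI takes 1, so about 7 to 8 out of about 800 once an added centre is allowed for. The variance inflation for the Cambridge indicator is about 1.4%, a negligible loss of precision, and the sample size need not change.

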### Study population

The inclusion and exclusion criteria for both donor subjects and controls are outlined in Table I and are identical to those set by the UK living kidney donor guidelines compiled by the Joint Working Party of The British Transplantation Society and The Renal Association.^31^ The only inclusion criterion is that donor subjects will be scheduled for nephrectomy for the purpose of kidney donation. A carefully matched series of control patients will be recruited from the same living donor clinics at which subjects are identified, who, after screening, are found to be fit for donation but do not proceed to surgery (eg, because of arterial anatomy and immunologic mismatch). If appropriate, donor-related family members will also be invited to participate in the study as healthy controls to provide a closely matched control population with equivalent baseline health status to the donor cohort.

**Table I t0005:** Inclusion and exclusion criteria

Inclusion criteria
Age 18-80 y
Acceptable GFR by donor age before donation⁎
Exclusion criteria
Hypertensive end-organ damage, uncontrolled hypertension or the requirement for >2 antihypertensive medications
Significant proteinuria†
LV dysfunction
Diabetes mellitus
Atrial fibrillation
Any history of cardiovascular or pulmonary disease that would preclude kidney donation

⁎ Based on the anticipation of having an eGFR of >50 mL/min per 1.73 m^2^ aged 70 years.

† ACR >30 mg/mmol, PCR >50 mg/mmol, or 24-hour total protein >300 mg/d.

Participants will be recruited from the following core centers, chosen because of their high numbers of live donor transplants and strength in vascular research: (1) Queen Elizabeth Hospital Birmingham, England; (2) Addenbrooke's Hospital, Cambridge, England; (3) Western Infirmary Glasgow, England; (4) University Hospital Coventry and Warwick, England; (5) Southmead Hospital, Bristol, England; (6) Northern General Hospital, Sheffield, England; and (7) Belfast City Hospital, Belfast, North Ireland. This study remains open to the inclusion of additional transplant centers from inside and outside the UK.

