Augmentation index and central hemodynamics	A micromanometer (SPC-301; Millar Instruments) will be used to flatten but not occlude the radial artery using gentle pressure. An averaged peripheral waveform and corresponding central waveform will be generated after 11 s of data capture. The central waveform will then be analyzed to determine augmentation index and central aortic pressures.
Renal function	Isotopic GFR using the renal clearance of ^51^Cr-EDTA will be measured in donors.
Bloods	Hemoglobin, creatinine, calcium, albumin, glucose, phosphate, PTH, NT-proBNP, and uric acid
Urine	ACR and fractional excretion of sodium

Abbreviations: *BHS*, British Hypertension Society; *EDTA*, ethylenediaminetetraacetic acid; *NT-proBNP*, N-terminal prohormone of brain natriuretic peptide.

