#### Assessment of renal function

Isotopic GFR for kidney donors will also be measured using the renal clearance of ^51^Cr-EDTA.^40^ Kidney function in controls will be estimated from serum creatinine measurement.^41^, ^42^

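### Isotopic GFR, measured only in donors, is listed as a covariate in the coprimary donor-versus-control model, with no stated way to enter it

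*Protocol article*

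**What the plan says.** The Statistical analysis section of the protocol article says that the formal comparison of the arms, for each coprimary end point, "will use a linear regression model on the within-patient change from baseline". Its covariate list includes "eGFR at donation (and iGFR where available in donors". The secondary analysis in the same paragraph words the GFR terms differently: "baseline eGFR and change in eGFR (and isotopic GFR where available in donors".

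The measurements behind these terms are described elsewhere in the article:

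- Table II, renal function row: "Isotopic GFR using the renal clearance of ^51^Cr-EDTA will be measured in donors".
- Assessment of renal function: "Isotopic GFR for kidney donors will also be measured using the renal clearance of ^51^Cr-EDTA", and then "Kidney function in controls will be estimated from serum creatinine measurement".
- Study population: the clinic controls are people who "are found to be fit for donation but do not proceed to surgery".
- Study protocol: investigations take place at the baseline visit in controls and in the six weeks before surgery in donors.

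So creatinine-based eGFR exists in both arms before surgery, and isotopic GFR exists in donors only.

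**The concern.** A covariate in a between-arm regression has to be defined in both arms. Isotopic GFR is absent from one arm by design, yet the sentence places it in the formal comparison. The analyst must therefore choose how to enter it. The obvious choices give different answers, from no estimate at all to an estimate shifted by a difference between laboratory methods.

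This model is the confirmatory analysis for both aortic pulse wave velocity (aPWV) and blood pressure. If the choice is made after the data are seen, the Holm-Bonferroni control of the 5% level no longer means what it claims. The words "eGFR at donation (and iGFR where available in donors" also date the eGFR covariate by an event that controls never have.

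**Working it through.** **1. The plan's own figures.** Inputs from the power section: SD of change 1.0 m/s, difference 0.22 m/s, two-sided 2.5%, power 80%.

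n per arm = 2 × (2.241 + 0.842)² × 1.0² / 0.22² ≈ 393, or 786 in total. The article states 400 per arm and 800 in total. Power at 400 per arm is 80.8% (normal) or 80.6% (t). Allowing for 9% dropout, 400 / 0.91 ≈ 440 per arm, which is the recruitment target. The blood pressure figures (2.2 over 10 mm Hg) have the same ratio and give the same n. The sample size is not in question.

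**2. Isotopic GFR as an ordinary added term, complete cases.** This needs no assumed numbers. All controls lack the variable, so the 400 remaining rows are all donors. The arm indicator then equals the intercept. With columns for intercept, arm, eGFR and isotopic GFR, the design matrix has rank 3 out of 4, and the arm effect is not estimable.

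**3. Other ways of entering GFR.** These need figures that the documents do not give. Assumed here:

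- true GFR with mean 90 and SD 14 mL/min in both arms;
- error SD 10 for eGFR and 4 for isotopic GFR;
- slope of aPWV change on true GFR −0.02 m/s per mL/min;
- isotopic GFR available in every donor.

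The simulation used 1,000 trials of 400 per arm, with a true arm effect of 0.22 m/s and total SD 1.0.

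| How GFR enters | Mean arm effect | SE |
|---|---|---|
| eGFR in both arms | 0.221 | 0.069 |
| eGFR plus isotopic GFR, 0 in controls | 1.03 | 0.367 |
| eGFR plus isotopic GFR centred within donors, 0 in controls | 0.219 | 0.069 |

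The second row fails because the arm coefficient becomes the effect at an isotopic GFR of zero. The shift of 1.03 − 0.22 = 0.81 is an isotopic GFR coefficient of about −0.009 carried over 90 mL/min. The SE grows by 0.367 / 0.069 ≈ 5.3 times.

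**4. Isotopic GFR replacing eGFR in donors.** No control is lost, but the measuring method now differs by arm. If isotopic GFR exceeds eGFR systematically by d, the arm estimate is about 0.22 − b × d, where b is the fitted GFR slope. Measurement error attenuates that slope:

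b = −0.02 × (196 + 196) / (212 + 296) = −0.02 × 0.772 = −0.0154,

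where 196 = 14², 212 = 14² + 4² and 296 = 14² + 10². The predicted shift is 0.0154 × 5 = 0.077 m/s for d = 5, and 0.154 m/s for d = 10. The simulation agrees:

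| Offset d (mL/min) | Arm estimate (true 0.22) | Type I error at nominal 2.5% |
|---|---|---|
| −10 | 0.07 | 44% |
| −5 | 0.14 | 11% |
| 0 | 0.22 | 2% |
| +5 | 0.30 | 14% |
| +10 | 0.38 | 47% |

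With half the slope (−0.01) and d = +10, the estimate is 0.30 and the type I error 13%.

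**5. After the change.** With eGFR in both arms all 800 subjects stay in the model, and simulated power is about 83%.

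**The case against.** Four points can be made for the plan.

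*The eGFR term works.* A reader might infer that the whole GFR adjustment fails because controls never donate. The documents do not support that. Controls have a creatinine-based estimate, and the baseline visit falls before surgery in donors. A reader might also fear that the covariate is a post-nephrectomy value, which would adjust away the exposure. That reading is strained, because the same paragraph speaks of baseline eGFR and lists the change in eGFR separately. This objection stands in full: the eGFR part is a fault of wording.

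*A working coding exists.* Isotopic GFR centred within donors, with 0 for controls, leaves the arm effect intact. So it would be wrong to say that the model must either drop the controls or bias the result. But the article does not state this coding. Because the measurement is planned only where available, donors without it would still drop out of a complete-case fit.

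*The bias figures belong to one reading.* The parenthesis says "and", which suggests addition rather than replacement. Under addition with complete cases the failure shows at the first fit and would not pass silently into a published estimate. That is fair. The substitution figures show what one plausible repair could cost; they do not predict what the trial will do.

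*It may be shorthand for a supplementary donor analysis, or be settled in a fuller plan.* Both are possible. Yet the sentence puts isotopic GFR in the formal between-arm comparison. The point is therefore a stated covariate that does not work in ordinary use, which is different from a detail left for later.

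**Conclusion.** The point holds for isotopic GFR and not for eGFR. As stated, the coprimary between-arm models include a covariate that one arm cannot have. With ordinary complete-case fitting the arm effect is not estimable, and this follows from the design alone. Zero coding makes the term nearly collinear with arm.

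Substitution biases the arm effect only if the two methods differ systematically. For assumed offsets of 5 to 10 mL/min in either direction and a slope of −0.02, the shift is about 0.08 to 0.15 m/s, or 35% to 70% of the 0.22 m/s target. With no offset there is no bias. The documents give neither the offset nor the slope, so these sizes are illustrative. They were worked for aPWV only, but the structural failure applies equally to blood pressure.

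**What to change.** In both coprimary donor-versus-control models, define the GFR covariate as baseline creatinine-based eGFR, by the same equation and at the baseline visit in both arms (before nephrectomy in donors). Remove isotopic GFR from the between-arm model. Use it in donor-only analyses, such as relating change in the end points to measured GFR, or in a labelled sensitivity analysis whose coding is written down beforehand, including how donors without a measurement are handled. Replace the reference to donation in the eGFR term with baseline.

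The cost is a line of wording, settled before outcome data are examined. No new measurement is needed, no subject is lost and the planned sample size stays as it is.

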### Hypotheses

In living kidney donors, the reduction in GFR that accompanies nephrectomy results in (1) a pressure-independent increase in aortic stiffness (aPWV), (2) an increase in blood pressure, (3) an increase in LV mass and impairment in LV diastolic function, and (4) adverse effects on bone mineral metabolism.

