#### Pulse wave analysis

Blood pressure measurement will be repeated supine before undertaking applanation tonometry to record high-fidelity arterial pressure waveforms from which indices relating to large artery stiffness can be calculated. Central pressure waveforms will be derived and analyzed using the technique of pulse wave analysis, as previously described.^35^, ^37^ A micromanometer will be used to flatten but not occlude the radial artery using gentle pressure. An averaged peripheral waveform and corresponding central waveform will be generated after 11 seconds of data capture. The central waveform will then be analyzed to determine the augmentation index (the difference between the second and first peaks of the central pressure waveform, expressed as a percentage of the pulse pressure) and central aortic pressures. The method has been shown to be reproducible in both healthy subjects and in patients with CKD. Augmentation index and aPWV will also be recorded using ambulatory measurements taken from the Mobilograph.^38^, ^39^

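### Hypothesis 1 is a pressure-independent rise in aortic stiffness, but the formal aPWV model adjusts only for baseline blood pressure and so estimates the total effect of donation

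*Protocol article*

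**What the plan says.** Under Hypotheses, the Protocol article sets out that the fall in GFR after nephrectomy leads to, among other things, "1) a pressure-independent increase in aortic stiffness (aPWV), (2) an increase in blood pressure". The abstract gives the same pair.

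Under Statistical analysis, each coprimary end point is compared between arms by "a linear regression model on the within-patient change from baseline", "adjusting for baseline value, sex, ethnicity, use of antihypertensives, age, eGFR at donation" (with isotopic GFR where available in donors) "and the other coprimary end point at baseline". For the aPWV model that last term is blood pressure, which Table II defines as mean 24-hour ambulatory systolic pressure.

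The same section adds: "Findings will be interpreted taking into consideration that aPWV and blood pressure are correlated". It also lists secondary analyses of the coprimary end points "according to age, ethnic group, baseline eGFR and change in eGFR", together with BMI and predonation hypertension. Change in pressure is not in that list.

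Under Pulse wave analysis: "Blood pressure measurement will be repeated supine before undertaking applanation tonometry". A pressure taken close to the stiffness measurement is therefore collected.

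**The concern.** Adjusting for baseline pressure removes differences between donors and controls that existed before surgery. It does nothing about pressure that changes afterwards. If donors' pressure has risen by 12 months and aPWV depends on the pressure at which it is measured, part of the rise in aPWV reflects the higher pressure, and the arm coefficient includes it.

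Hypothesis 2 predicts exactly this rise, so the gap opens in the scenario the study expects. At stake is the qualifier in hypothesis 1. The total effect of donation on aPWV is a legitimate causal quantity and worth testing. It is a different quantity from a pressure-independent effect.

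The distortion could also run the other way. Under Study protocol, new treatment, including antihypertensive drugs, is unrestricted, so follow-up pressure may fall in some participants and hide part of a pressure-independent rise.

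**Working it through.** **Inputs from the Protocol article** (EARNEST power calculations and sample size, unless noted)
- SD of within-patient change: 1.0 m/s for aPWV, 10 mm Hg for blood pressure.
- Detectable differences: 0.22 m/s and 2.2 mm Hg.
- 400 per arm after 9% dropout, 80% power, two-sided 2.5% level.
- Rise of about 5 mm Hg in systolic pressure at 10 years after donation (Background and rationale).
- Follow-up at 12 months (Study protocol).

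**Assumption, not in the documents:** aPWV rises by 0.02-0.05 m/s per mm Hg.

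**Step 1: the plan's own figure.** n per arm = 2 × (2.241 + 0.842)² × 1.0² / 0.22² = 393. The blood pressure figures give the same ratio (2.2/10) and the same n. With 400 per arm the power is 80.8%. Allowing for dropout, 400/0.91 = 440, the recruitment target. The stated sample size reproduces.

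**Step 2: what the planned arm coefficient estimates.** With only baseline pressure in the model,

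arm coefficient = pressure-independent effect + slope × (donor minus control difference in pressure change).

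Set the first term to zero. The standard error is √(2/400) = 0.0707 m/s. The rejection probability is Φ(d/0.0707 − z) + Φ(−d/0.0707 − z), where d = slope × pressure rise and z = 2.241 at the 2.5% level. Example: 2.2 × 0.05 = 0.11 m/s; 0.11/0.0707 = 1.556; Φ(1.556 − 2.241) = 24.7%.

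| Pressure rise (mm Hg) | Slope (m/s per mm Hg) | d (m/s) | Rejects at 2.5% | Rejects at 5% |
|---|---|---|---|---|
| 2.2 | 0.02 | 0.044 | 5.5% | 9.5% |
| 2.2 | 0.03 | 0.066 | 9.6% | 15.4% |
| 2.2 | 0.05 | 0.110 | 24.7% | 34.3% |
| 5 | 0.02 | 0.100 | 20.4% | 29.3% |
| 5 | 0.03 | 0.150 | 45.2% | 56.4% |
| 5 | 0.05 | 0.250 | 90.2% | 94.2% |

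The 5% column is shown because Holm-Bonferroni tests aPWV at 5% once blood pressure has been declared significant first. At 2.2 mm Hg, the pressure-driven part is 0.044/0.22 = 20% to 0.11/0.22 = 50% of the target difference.

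Outside the assumed range, a slope of 0.01 gives 3.2% (2.2 mm Hg) and 6.4% (5 mm Hg) at the 2.5% level. A slope of 0.10 gives 81% and about 100%.

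**Step 3: simulation.** There were 2,000 runs per scenario with 400 per arm, the SDs above, and an effect acting only through pressure. The planned adjustment rejected in 4.6% and 25.4% of runs at 2.2 mm Hg (slopes 0.02 and 0.05), and in 20.1% and 89.9% at 5 mm Hg. At 5 mm Hg and 0.05 its mean arm estimate was 0.248 m/s, above the 0.22 m/s target. With change in pressure added, that mean estimate was about zero, and rejection was 2.0-2.8% over slopes of 0.02, 0.05 and 0.08, against a nominal 2.5%.

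**The case against.** A reader might infer that a purely pressure-driven rise would be reported as confirming hypothesis 1. The article does not support that: it commits to interpreting the findings in the knowledge that the two end points are correlated. What stands is that this commitment comes with no estimate and no rule.

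A reader might also infer that hypothesis 1 cannot be answered. That is too strong. Blood pressure is a coprimary end point in the same participants. If it does not rise, little of an aPWV difference can be attributed to pressure. The supine pressure needed for an adjusted analysis is collected, so the weakness lies in what is prespecified, not in the design.

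The analysis plan is not shown and may contain a supporting model. But the article does not leave this point open. It states the formal comparison, lists the covariates, fixes the other end point at its baseline value, and lists secondary analyses that include change in eGFR but not change in pressure. The mismatch between hypothesis and formal model is on the page.

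The percentages deserve caution, and this objection stands. They all depend on an assumed slope. The 5 mm Hg figure belongs to 10 years after donation, not 12 months. The 2.2 mm Hg figure refers to ambulatory systolic pressure, whereas the pressure nearest the measurement is supine. The calculation also ignores antihypertensive treatment. Use of antihypertensives is a covariate, but its timing is not stated and it does not stand in for follow-up pressure.

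**Conclusion.** The point holds, as something that should be fixed. The formal model estimates the total effect of donation on aPWV, while hypothesis 1 concerns the pressure-independent part. The two differ whenever pressure changes differently in donors and controls, and hypothesis 2 predicts that it will. This conclusion does not depend on any assumed number.

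The size does. With no pressure-independent effect and a slope of 0.02-0.05 m/s per mm Hg, the 2.5% test rejects in about 6-25% of trials at a 2.2 mm Hg rise. It rejects in 20-90% at 5 mm Hg, which is an upper scenario for a 12-month study. At the low end the excess over 2.5% is small.

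The sample size, the multiplicity procedure and the stated test of the total effect are not called into question here.

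**What to change.** Keep the stated model and label it the total-effect analysis. Prespecify a second aPWV model with the same covariates plus the change, from baseline to 12 months, in supine blood pressure measured at the tonometry visits (mean arterial pressure if it can be derived).

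State that a result will be called pressure-independent only if the confidence interval for the arm effect in this second model lies wholly above zero. The interval should be at the level used for the aPWV test: 97.5% if aPWV is tested at 2.5%, 95% if Holm-Bonferroni has moved it to 5%.

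The cost is one regression on data already collected and a sentence on interpretation; the sample size need not change. The downside should be written beside it. The second model conditions on a post-donation variable and assumes no unmeasured confounding between change in pressure and change in aPWV. If stiffening itself raises pressure, the adjustment may remove part of the true effect. The simulation above does not test that last case, because pressure was the only route in it. For these reasons the second model should accompany the total-effect analysis, not replace it.
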